## Abstract

**Background:**

Addressing adolescent pregnancies associated health burden demands new ways of organizing maternal and child mental health services to meet multiple needs of this group. There is a need to strengthen integration of sustainable evidence-based mental health interventions in primary health care settings for pregnant adolescents. The proposed study is guided by implementation science frameworks with key objective of implementing a pilot trial testing a full IPT-G version along with IPT-G mini version under the mhGAP/IPT-G service framework and to study feasibility of the integrated mhGAP/IPT-G adolescent peripartum depression care delivery model and estimate if a low cost and compressed version of IPT-G intervention would result in similar size of effect on mental health and family functioning as the Full IPT-G. There are two sub- studies embedded which are: 1) To identify multi-level system implementation barriers and strategies guided by the Consolidated Framework for Implementation Research (CFIR) to enhance perinatal mhGAP-depression care and evidence-based intervention integration (i.e., group interpersonal psychotherapy; IPT-G) for pregnant adolescents in primary care contexts; 2) To use findings from aim 1 and observational data from Maternal and Child Health (MCH) clinics that run within primary health care facilities to develop a mental health implementation workflow plan that has buy-in from key stakeholders, as well as to develop a modified protocol and implementation training manual for building health facility staff’s capacity in implementing the integrated mhGAP/IPT-G depression care.

**Methods:**

For the primary objective of studying feasibility of the integrated mhGAP/IPT-G depression care in MCH service context for adolescent perinatal depression, we will recruit 90 pregnant adolescents to a three-arm pilot intervention (unmasked) trial study (IPT-G Full, IPT-G Mini, and wait-list control in the context of mhGAP care). Pregnant adolescents ages 13–18, in their 1st-2nd trimester with a depression score of 13 and above on EPDS would be recruited. Proctor’s implementation evaluation model will be used. Feasibility and acceptability of the intervention implementation and size of effects on mental health and family functioning will be estimated using mixed method data collection from caregivers of adolescents, adolescents, and health care providers. In the two sub-studies, stakeholders representing diverse perspectives will be recruited and focus group discussions data will be gathered. For aim 2, to build capacity for mhGAP-approach of adolescent depression care and research, the implementation-capacity training manual will be applied to train 20 providers, 12 IPT-G implementers/health workers and 16 Kenyan researchers. Acceptability and appropriateness of the training approach will be assessed. Additional feedback related to co-located service delivery model, task-shifting and task-sharing approach of IPT-G delivery will be gathered for further manual improvement.

**Discussion:**

This intervention and service design are in line with policy priority of Government of Kenya, Kenya Vision 2030, World Health Organization, and UN Sustainable Development Goals that focus on improving capacity of mental health service systems to reduce maternal, child, adolescent health and mental health disparities in LMICs. Successfully carrying out this study in Kenya will provide an evidence-based intervention service development and implementation model for adolescents in other Sub-Saharan African (SSA) countries. The study is funded by FIC/NIH under K43 grant.

## Background

Globally depression is the leading cause of disease burden in women of reproductive age. Maternal depression occurs in women during both antenatal and postnatal periods. The prevalence of depression is high among pregnant women, with worldwide estimates of 11% to 18% [1, 2] and is estimated to be between 15% to 28% in Lower- and Middle-Income Countries (LMICs) [3]. Studies in Kenya and neighboring countries have found that younger women (aged 18–24 years) experience greater psychological vulnerabilities [4] and depression in this group ranges from 8.3% to 39% [5–7] with high risk populations like adolescent mothers and gender-based violence impacted women [8]. Young women in Sub-Saharan Africa (SSA) lose around 10.4 disability adjusted life years due to depression during pregnancy. Women who experience antepartum depression often continue to experience depressive symptoms into the postpartum period, with more than 54% of those with postpartum depression reporting depressive episodes before or during pregnancy [9]. Pregnant women between ages 18–21 years are at high risk for depression in countries like Kenya because circumstances that lead to their pregnancy often include low socioeconomic status and food insecurity [10], with subsequent increases in unprotected sex with older men in an effort to seek financial support through sexual favors. These economic factors also contribute to early motherhood, gender-based violence, low educational attainment and social stigma, all of which are associated with higher prevalence of depression [8, 11–16]. These vulnerable young women need health care and psychosocial support in building resilience against challenging barriers and risk factors.

Consistent with the World Health Organization (WHO) recommendations for LMICs, we propose Interpersonal Psychotherapy (IPT), an evidence-based depression treatment with demonstrated clinical efficacy in East African regions of Kenya and Uganda, for young women’s depression during pregnancy [17, 18]. IPT has demonstrated high efficacy when delivered by a readily available workforce of local, non-specialist personnel in East Africa [17, 19–22]. Based on recent studies utilizing IPT-G in Kenya [18, 23], we believe that IPT’s focus on social support, rebuilding interpersonal relationships by bolstering interpersonal communications skills, and focusing on life-transitions make it a promising fit with the mental health care needs of pregnant adolescents. However, pregnant adolescents in Kenya experience a particular set of stressors which we believe will require adaptation of standard IPT in order to match this particular population’s needs. For example, pregnant adolescents and adolescent mothers in Kenya are often unable to complete education as planned with related shortcomings in earning potential and are susceptible to exploitation and abuse by their biological families and community in general. While IPT is well-equipped to address most of these issues, some adaptations are necessary to address specific role transitions, adverse life circumstances and losses faced by young pregnant adolescents and women in Kenya.

### Adolescent pregnancies and unmet adolescent needs in Kenya

Adolescents make up nearly 16% of the world’s population, and the proportion is greater in Sub-Saharan Africa (23% of the regional population) [24]. Over 16 million adolescent girls worldwide give birth between ages 15–19, and the vast majority of these births (95%) occur in LMICs [25]. When adolescent girls become mothers, their opportunities for economic and educational growth are compromised. A burgeoning number of adolescent mothers from LMICs are marginalized due to poverty, gender-based traditions or geographical resource scarcity which further limit their access to health resources, information, social protection, and personal development [1, 10, 26–29]. Structural inequalities and adverse circumstances have detrimental impact on adolescent mothers’ mental health and this sets the stage for adverse medical conditions, risky behaviors, and mental illness in adulthood [27, 30]. Estimated prevalence of depression during perinatal period is 11% to 18% worldwide and between 30% to 50% in LMICs [1, 31–33]. The risk for perinatal depression in adolescents is 2 to 9 times higher than adults [2, 31, 33–35]. Despite the enormous mental health needs for adolescent mothers in LMICs, perinatal mental health research has focused on adults and has not considered the unique challenges that adolescent mothers are facing. Most research has also not invested in public health strategies or culturally relevant strategies to empower adolescents and address the mental health resource and service gaps for this population in LMIC settings.

### Global mental health service strategies and agenda for addressing needs in LMIC settings

WHO proposed two comprehensive frameworks for supporting efforts to establish and scale-up mental health services in LMICs. The Comprehensive Mental Health Action Plan (MHAP) 2013–2020 (or the Action Plan) [34] proposes system strengthening in 4 areas to improve population mental health: i) developing effective leadership and governance, ii) providing comprehensive, integrated, and responsive mental health services, iii) implementing strategies for promoting mental health, and iv) strengthening evidence and research for mental health. The Mental Health Gap Action Programme (mhGAP) [35, 36] focuses on ii) and iii) of the MHAP and further provides evidence-based guidelines and tools to support service system setup, delivery, and provision of evidence-based interventions (EBIs) for common mental health disorders in health care settings with limited specialty [37]. MHAP is a World Health Assembly approved policy document while mhGAP Intervention Guidelines (mhGAP-IG) are evidence-based guidelines and supportive technical material. mhGAP material helps member states to achieve the objectives of MHAP. Specifically, mhGAP recommends applications of collaborative, task-shifting, and task-sharing implementation strategies (i.e., considering collaboration between mental health specialists and non-specialist health-care providers and redistribution of clinical tasks from mental health specialists to non-specialized providers) in provision of mental health services. The mhGAP-IG also provides assessment, management clinical decision-making action flowcharts, and recommended EBIs for treating 8 priority mental health conditions (including interventions for depression). Although both MHAP and mhGAP have been applied successfully to address adult depression and other mental disorders in several LMICs [20, 38, 39], application of these frameworks in child and adolescent mental health service and in Kenyan contexts remains in infancy. A handful of depression intervention studies in LMICs that use EBIs recommended in the mhGAP (e.g., Group interpersonal psychotherapy/IPT-G, Thinking Healthy Program, Problem Management Plus) have exclusively either focused on perinatal depression for a wide range of reproductive-aged women [15, 27, 40–44] or interventions for depressed adolescents in non-medical health service settings [17, 45]. Most studies have focused on efficacy of EBIs and have not examined implementation related questions or tested feasibility of mhGAP-IG for peripartum adolescent mental health. More pragmatic research that simultaneously considers effective mental health leadership development, workforce development strategies, EBI implementation strategies, and effectiveness outcomes is sorely needed.

In considering utilizing WHO recommended models to adolescent perinatal depression in Kenya, several other system and service level implementation gaps and adolescent population characteristics need to be considered. Like other LMICs, Kenya has weak child and adolescent mental health system with limited mental health professionals and workers [17]. In tandem with the global agenda, the Kenya Vision 2030 mental health policy program (developed in 2012) brings in major health system reforms aiming at ensuring equity, people centeredness and participatory approach, efficiency, multi-sectoral approach and social accountability in delivery of mental health services [46]. However, progress in actualizing these changes in child mental health policy and service system development remain slow.

In addition to the systemic gaps, other intervention-implementation research gaps exist. First, in *the current mhGAP-IG, evidence-based guidelines and tools for adult depression (including perinatal depression) and child and adolescent depression are separated*, but interventions that integrate both pregnancy and adolescent needs for adolescent perinatal depression are lacking. The adult and child/adolescent versions of mhGAP-depression packages focus on different contents and approaches. For example, in adult depression, mhGAP-IG emphasizes on patient’s individual needs and intervention (i.e., psychoeducation, stress reduction and strengthening social support, promoting improved functioning in daily activities, brief psychological treatment for depression, and pharmacology). For adolescent depression, mhGAP-IG considers critical roles of caregivers, families, and schools/teachers in depression intervention given adolescents’ developmental needs; therefore, it recommends that depression intervention for adolescents must consider both individual and family/community related intervention (i.e., consideration of psychoeducation for the child/adolescent and family, guidance on promoting wellbeing, caregiver support, stressors management, community resources linkage, and collaboration with teachers/schools in managing depression). Although both adult and child/adolescent depression intervention guidelines/tool packages are relevant to adolescent perinatal depression, how these packages should be adapted to effectively address Kenyan perinatal adolescent needs is yet to be systematically studied. *Another gap is the demand-resource gap*, as maternal and child health (MCH) clinics usually serve high volume of pregnant adolescents or young mothers (e.g., 20–30 pregnant adolescents are seen per week [or 960–1440 per year] in each MCH clinic in Nairobi, Kenya). Considering high prevalence of adolescent pregnancy, high risk for depression in this population, and low resource in MCH clinics, utilizing WHO recommended depression EBIs (e.g., IPT-G), which usually require more than 5 intervention sessions, may not be practical in meeting population service demands and needs. Additional cost-effective strategies (such as considering lower dose implying fewer intervention sessions, using group instead of individual approach for intervention, applying low-cost patient/family/community empowerment approaches of service provision) would be needed.

In summary, given varied developmental needs and living context differences (e.g., parent-child co-living, connection with educational institutions) between adults and adolescents, more intervention implementation-effectiveness research for perinatal depression in adolescent population is needed. In addition, given the utility, comprehensiveness, and potential impacts of mhGAP, systematically studying the feasibility of integrating mhGAP in routine MCH care for adolescents with perinatal depression merits further inquiry. These areas of research will provide knowledge for providing integrated intervention (or co-located MCH and mental health services) to reduce burden of perinatal depression for adolescents in Kenya and LMIC in general.

Given this background, the purpose of this study is to identify strategies to improve integration and fit of the mhGAP-depression intervention model (including IPT-G) for pregnant adolescents in Kenya; to develop a Kenyan-adolescent version of WHO recommended mhGAP/IPT-G intervention program and training manual for intervention implementation and service system capacity building; and to pilot test feasibility of this integrated mhGAP/IPT-G service delivery model for adolescent prenatal depression (see Fig. 1 and Tables 1, 2, 3).

**Fig. 1 Fig1:**
[figure not shown]
CONSORT for mhGAP/IPT-G Randomized Pilot Feasibility Study

**Table 1 Tab1:** Summary table the pilot feasibility trial

Objectives	Outcomes	Criterion for success	Method for analysis	Estimate of effect
Primary feasibility	Demonstrate that the method of RCT feasible in MCH clinical service context	70% of pregnant adolescent-caregiver-health care workers that are exposed to content of the intervention; 80% of data collection performed as planned;	Quantitative analysis for implementation outcomes will be based on data collected throughout the implementation period, and analyzed separately for each time point as well as jointly to create overall summary scores. Analysis for the MCH service outcomes will be based on pre-post intervention data using pair-t tests and repeated measures. Quantitative data for implementation outcomes, MCH service outcomes, and adolescent mental health effectiveness outcomes will be examined separately. Qualitative data will be transcribed and analyzed using similar techniques described in Aim 1. We will review all focus group discussion data and use grounded theory approach to search for emerging themes using open and axial coding.	Depression and family functioning will be based on multi-level modeling, adjusting for family/group nesting effects. Post-intervention effects estimated as a function of baseline levels of the corresponding outcome variables and intervention status.
Secondary outcomes	a) Identification of barriers and facilitators to mhGAP/IPT-G implementation in MCH context b) Capacity building of MCH personnel, researchers and select MOH and County health partners c) Adaptation of mhGAP/IPT-G	a. Identification of select mhGAP informed barriers to care and adaptation of mhGAP and IPT-G for this context b. Capacity building will significantly improve trainees’ (nurses and community health workers) knowledge and skills in implementation research and delivering of depression intervention. c. Adapted manual for IPT-G and algorithm for mhGAP-IG for depression for pregnant adolescents	Qualitative and ethnographic methods including mixed methods using D& I and attitudes to EBI and adolescent friendly health services Pre and post training interviews and acceptability and satisfaction the trainings Knowledge and fidelity trainings on mhGAP/IPT-G	N/A

**Table 2 Tab2:** Study measures for the feasibility evaluation study: constructs, informants, assessment schedule, and assessment tools (to accompany the SPIRIT figure)

Constructs, informant, & assessment time	Assessment tools/measures
**Multi-level D&I Context (domains listed in** Fig. 1**)** [Time 1]	
**Inner setting &Individual Characteristics (MCH staff, Adolescent reports)):** * MCH system characteristics; * Implementer demo & attitude about the EBI; * Family characteristics	Provider Environment Questionnaire Survey [45, 47]; Organization climate/Readiness Questionnaire [47]; EBP Attitude Scale [46]; Family Demographics /Social determinants
**mhGAP/IPT-G Implementation Feasibility Outcomes** [Assessed Throughout Implementation Period]	
**a) Fidelity (Staff):** Feasibility in implementing mhGAP service delivery model and delivering > 80% of session content in MCH setting; **b) Engagement (staff report)**: Feasibility in reaching the targeted population (adolescent-parent pairs), and maintain high program participation/session attendance; **c) Quality of Implementation (adolescent-report)**: *****Acceptability, Appropriateness Usefulness, Satisfaction (of IPT-G implementation procedures and contents);	**a**: Fidelity Checklists **b:** Program Engagement, attendance; **c.** Acceptability, Appropriateness, Usefulness, Satisfaction;
**MCH Mental Health Service Outcomes** [Time 1, Time 2]	
**a) MCH service quality (adolescent mothers):** patient satisfaction of the integrated mental health & MCH care**;** **b) MCH climate (staff & adolescent report)**: support, trust, communication about adolescent health; responsive adolescent services.	**a:** Service quality; **b:** Organization Climate Questionnaire [47]
**mhGAP/IPT-G trial design feasibility and effect size estimation for mental health & family functioning outcomes** [Time 1, Time 2]	
a) **Design feasibility:** is the method of RCT feasible in MCH clinical service context **b) Estimated size of effect on adolescent mental health (adolescent report);** **c) Estimated size of effect on family functioning (adolescent & caregiver report):** functioning, depression, trauma, adjustment, social support, self-efficacy, stress, family interpersonal communication.	**a:** % of adolescent-caregiver pairs that are exposed to content of the intervention; % of data collection performed as planned; **b**:WHO-Disability Assessment Schedule; Edinburgh Postpartum Depression Scale; Patient Health Questionnaire-9;**c:** Self-efficacy; Social support; PTSD Patient Checklist-Civilian; Kessler Psychological Distress Scale; Adolescent Interpersonal Connectedness and Conflict Inventory [48–55]

Note. The primary outcomes for this pilot feasibility study are mhGAP/IPT-G effectiveness outcomes

Implementation and service outcomes are the intermediate or secondary outcomes of this study

**Table 3 Tab3:** Information about the technical and community advisory boards

Community Advisory Board will include the following representatives: − 6 MCH (2 leader/directors, 2 nurse, 2 CHW) − 2 governmental (1 MoE, 1 MoH) − 2 academics (1 health service/implementation, 1 clinical researcher) − 2 advocacy (2 representative NGO leader) − 5 community stakeholders (2 caregivers of pregnant adolescent, 3 adolescent representatives). The technical advisory board comprises of following members: -UNFPA program officer (responsible for sexual and reproductive health issues, working on adolescent girl child mental health. - Director, mental health services, MoH (responsible for integrating mhGAP in clinical workflow at primary care level) - Research officer, Nairobi County Health Directorate (Responsible for task sharing and stigma reduction strategies to address depression) -WHO, Kenya county office -Mental health focal officer (Responsible WHO mhGAP adaptation and local capacity building in mental health) -WHO HQ Geneva (Responsible for G-IPT adaptation and mhGAP for adolescent peripartum depression management) -UNICEF Regional office- MCH and adolescent health program officer advise on MCH and adolescent mental health policy and programs)	

The adolescent version of mhGAP/IPT-G is yet to be developed in Kenya. We are proposing a pilot study to test feasibility of the trial study design and estimate size of mhGAP/IPT-G intervention effects (Full and Mini versions) on pregnant adolescents’ mental health and family functioning.

As a first step, we will bring a group of leaders/stakeholders from MCHs and communities together to focus on:
strategies to enhance the fit of mhGAP/IPT-G into Kenyan pregnant and parenting adolescents’ needs as well as MCH clinical structure, resources, and workflow (in addition to the task-shifting/sharing and collaborative strategies that have been included as part of the mhGAP);strategies for designing adolescent version of mhGAP/IPT-G training manual and effective capacity building approach to support the implementation of the integrated mhGAP/IPT-G service delivery in MCHs.

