#### Intervention implementation

Participants will be randomly assigned to IPT-G Full, IPT-G Mini, and wait-list control using computer random generator by research staff (*n* = 15 for each arm, 45 per cohort).
The IPT-G Full and Mini groups will receive the assigned interventions (8 vs. 4 sessions) developed from Aims 1 and 2 (including a perinatal depression educational material/handout). To avoid contamination, intervention for the IPT-G Full and Mini versions will be carried out by 2 separate implementation teams (2–3 facilitators in each team) follow the assigned manual/protocol. Figure 2 provides intervention contents for the Mini version, in comparison to the recommended Full version.The Control will receive standard care (with referral) and perinatal depression educational materials for safety concerns. They will receive IPT-G Mini after the post implementation assessment is completed.

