#### Feasibility evaluation measures and procedure

To evaluate feasibility of the mhGAP-IG/IPT-G implementation model in the MCHs, a mixed methods data collection approach will be applied and data will be collected from multiple sources (i.e., implementers, MCH leaders, adolescent mothers and their family members) to minimize data collection bias. As described above, the *Conceptual model of Implementation Outcomes* [56] is applied to guide the construct selection for the implementation feasibility and impact estimation. Feasibility of the mhGAP/IPT-G mental health service delivery model will be assessed using three indicators: fidelity (i.e., % of sessions is delivered with > 80% of contents), level of engagement (e.g., % reach targeted population, % participating in intervention sessions), quality of implementation (e.g., acceptability, appropriateness, usefulness, satisfaction of the mhGAP/IPT-G service model), and perceived mental health service (e.g., mental health service quality, MCH climate). Feasibility of applying a trial design for mhGAP/IPT-G impact evaluation in MCHs will be assessed using two indicators: % of adolescent-caregiver pairs that are exposed to intervention contents within the assigned condition; and % of data collection performed as planned. Impacts/effect size estimation for the IPT-G Full and Mini versions (the secondary outcomes) will be assessed for adolescents’ mental health and family functioning outcomes. Both quantitative data and qualitative data will be collected. Qualitative data will be collected through focus groups (2 groups for each intervention arm) at the end of implementation cycle. Tables 1 and 4 lists the feasibility outcomes measures and sources of data collection (under implementation feasibility, mental health service outcomes, and trial design feasibility and effect size estimation). Implementation feasibility outcome data, collected from the MCH staff/intervention implementers and adolescents who participated in the two intervention arms (IPT-G Full and Mini), will be gathered after each group session throughout the two implementation periods. For effect-size estimation, all study participants will complete a baseline (Time 1) interview (on mental health and family functioning outcomes) before randomization and intervention implementation, followed by a 1- or 2-month implementation period (2 months for the IPT-G Full and 1 month for the IPT-G Mini). Only when a participant is physically unwell, or has to terminate due to a pregnancy related emergency or any other severe mental health issue will their participant grouping be unblinded and an appropriate referral made. They will receive a post-intervention interview assessment at the end of implementation cycle (Time 2, about 3–4 months after the Time 1). To facilitate coordination of program implementation activities, participating MCH will be provided with two tablets and a small incentive which could offset implementation costs.

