#### Analysis plan for the feasibility outcomes

Data collected through 2 cohorts will be analyzed. Quantitative analysis will be focused on examining the following questions:
Examine acceptability, appropriateness, usefulness, engagement, and fidelity for both full and mini versions of integrated mhGAP/IPT-G intervention implementation using task-shifting/sharing approach in MCH contexts.Examine MCH service quality change patterns before and after implementation of the mhGAP/IPT-G model will improve.Examine whether pregnant adolescents in the IPT-G will have better outcomes relative to control, but high impacts/effect size for the IPT-G Full version.

The following stop-go criteria will be used to determine whether to proceed to the main trial: the recruitment proceeds well so that the first IPT-G cohort can proceed by the end of the first month of the specified recruitment period. The IPT therapists that is the trained CHVs and nurses demonstrate adequate levels of treatment fidelity to the WHO IPT-G checklist adherence available in the manual and 70% of participants attend at least 5 of the available sessions in the course of their treatment and 80% are successfully followed up at primary endpoint.

Quantitative analysis for *implementation outcomes* will be based on data collected throughout the implementation period, and analyzed separately for each time point as well as jointly to create overall summary scores. Analysis for the *MCH service outcomes* will be based on pre-post intervention data using *paired-t tests* and repeated measures. We will examine patterns separately and jointly for two MCH clinics. Analysis for *estimating size of impact* on mental health (depression) and family functioning will be based on multi-level modeling, adjusting for family/group nesting effects. Post-intervention effects/impacts will be estimated as a function of baseline levels of the corresponding outcome variables and intervention status. Effect size (regardless the statistical testing significant level) will be computed. *Quantitative data* for implementation outcomes, MCH service outcomes, and adolescent mental health effectiveness outcomes will be examined separately.

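### Table 1 and the stop-go rule give different, unreconciled success criteria for the pilot, and perfect delivery can pass one and fail the other

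*Protocol article*

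**What the plan says.** The protocol article describes the success of this pilot in four places.

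- **Table 1, primary feasibility row.** The outcome is "Demonstrate that the method of RCT feasible in MCH clinical service context". The criterion for success is "70% of pregnant adolescent-caregiver-health care workers that are exposed to content of the intervention; 80% of data collection performed as planned". No denominator is given, and no minimum amount of content that counts as exposure.
- **Feasibility evaluation measures and procedure.** The exposure indicator for trial-design feasibility is the percentage "of adolescent-caregiver pairs that are exposed to intervention contents within the assigned condition". The unit is now the pair, without the health worker.
- **Table 2, design feasibility.** Pairs again, without a denominator.
- **Analysis plan for the feasibility outcomes.** "The following stop-go criteria will be used to determine whether to proceed to the main trial": recruitment must be fast enough for the first cohort to start by the end of the first month; the therapists must "demonstrate adequate levels of treatment fidelity to the WHO IPT-G checklist adherence". The remaining two conditions read: "70% of participants attend at least 5 of the available sessions in the course of their treatment and 80% are successfully followed up at primary", with the endpoint as the point of follow-up. The unit is the participant.

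Under Intervention implementation, Full has 8 sessions, Mini has 4, and each arm has 15 participants per cohort. Controls get standard care and educational material during the comparison period. Of IPT-G for controls the article says: "They will receive IPT-G Mini after the post implementation assessment is completed".

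**The concern.** A pilot's success criteria are useful only if they are fixed and lead to one answer. Here two sets carry the same pair of percentages, 70 and 80, and so look like one rule stated twice. They measure different things. Any contact with intervention content is a much lower bar than attending 5 sessions. Completing the planned data collection is not the same as follow-up at an endpoint. The article names the stop-go rule as the one that decides on a main trial. It does not say how a pilot should be reported that meets Table 1 and fails the stop-go rule, or the reverse. If that happens, the team has to settle after seeing the data which statement to rely on and which denominator was meant.

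**Working it through.** **Inputs.** 15 per arm per cohort, 3 arms and 2 cohorts (Intervention implementation; Analysis plan for the feasibility outcomes). Sessions: Full 8, Mini 4. Controls receive no IPT-G before Time 2 and Mini afterwards.

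**The plan's own figure.** 15 × 3 × 2 = 90, which reproduces the stated total, with 15 × 2 = 30 per arm. The sample size rests on a rule of 30 per arm, so there is no power calculation to check.

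**The two rules side by side.**

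| | Table 1 | Stop-go rule |
|---|---|---|
| Unit | adolescent, caregiver and health worker (pairs in Table 2 and in the measures section) | participant |
| 70% bar | exposed to content, no minimum | at least 5 sessions attended |
| 80% bar | planned data collection carried out | followed up at the endpoint |
| Further conditions | none | recruitment timing, fidelity |
| Denominator | not stated (within the assigned condition, in the measures section only) | not stated |

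**Perfect delivery.** Suppose all 30 Full participants attend 8 sessions and all 30 Mini participants attend 4.

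- Exposure, over the two IPT-G arms: (30 + 30)/60 = 100%. The 70% bar needs 42 of 60, so it passes.
- At least 5 sessions, over the two IPT-G arms: (30 + 0)/60 = 50%. The bar needs 42 of 60, so it fails.
- At least 5 sessions, over all randomised: 30/90 = 33.3%. The bar needs 63 of 90, so it fails. Counting the controls' later Mini sessions changes nothing, because these are also only 4.
- At least 5 sessions, over Full alone: 30/30 = 100%. It passes.

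The attendance bar is thus out of reach on any denominator that includes the Mini arm. Even on the Full arm alone the rules can part: if all 30 attended 4 of their 8 sessions, exposure would be 30/30 and attendance of at least 5 would be 0/30.

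**Highest possible exposure under Table 1, counting adolescents.**

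- All randomised, only IPT-G before Time 2 counted: 60/90 = 66.7%, below 70% (63 needed).
- Full and Mini arms only: 60/60 = 100%.
- All randomised, with the controls' later Mini counted: 90/90 = 100%.

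**The case against.** The two statements may serve different purposes. Table 1 asks whether a randomised trial can be run in these clinics, and only the stop-go rule is said to decide on a main trial. On that view there is no open choice about which set governs progression. This stands in part: that both serve one decision is an inference. But both declare when this pilot's feasibility has been shown, with the same percentages, and nothing says how they relate. The shift from triads in Table 1 to pairs in Table 2 and the measures section occurs within trial-design feasibility itself, so a difference in purpose cannot explain it.

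Three stronger readings are tempting and are not supported.

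- A reader might infer that the Table 1 exposure bar cannot be reached, since a third of those randomised get no IPT-G before Time 2. That needs all 90 as denominator and only pre-Time 2 IPT-G as exposure. The article states neither, and its phrase about the assigned condition allows 60/60. The defect is an undefined denominator.
- A reader might infer that the 80% follow-up bar is pooled over arms and so hides unequal dropout. The article says only "80% are successfully followed up at primary endpoint" and does not say whether this is pooled or by arm. An article may leave that to the full protocol or SAP.
- A reader might want 24 of 30 followed up in every arm as the pass mark. That is a real trade-off. Assuming a true retention of 85% in each arm, independent between participants, the chance of at least 72/90 overall is 0.93, while the chance of at least 24/30 in all three arms is 0.61.

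**Conclusion.** The point holds as an inconsistency between two stated sets of success criteria. They agree on 70% and 80% and differ in unit, measure and denominator. Its size is shown by the extreme case: with flawless delivery, exposure is 100% of the IPT-G arms, while stop-go attendance is at most 50% of those arms and 33% of all randomised. This uses only the article's own allocation and session counts, and assumes that the attendance criterion is meant to cover the Mini arm, which the word participants suggests and nothing excludes. The 66.7% ceiling on exposure is one reading of an open denominator and should not be reported as a bar that cannot be met. The plan should be corrected before the pilot is judged, because the wording alone can decide its conclusion.

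**What to change.** Use one criteria set and print it in identical words in Table 1 and under Analysis plan for the feasibility outcomes, with Table 2 and the measures section brought into line.

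- **Unit:** the randomised adolescent, with caregiver participation reported separately.
- **Exposure denominator:** those randomised to Full or Mini, reported by arm, with a statement of what counts as exposure.
- **Attendance:** reconcile the 5-session criterion with the 8- and 4-session schedules under Intervention implementation, so that each IPT-G arm is able to meet it. The threshold itself is for the investigators to set.
- **Follow-up:** keep the overall 80% bar and tabulate follow-up by arm, without a pass/fail bar per arm.
- **Recruitment and fidelity:** carry these conditions into Table 1 as well, so that the two lists match.

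The cost is rewording and one by-arm tabulation. Sample size, visits and data collection do not change.
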